***Secondary outcomes***

**TCM Syndrome Scoring System**

### TCM Syndrome Scoring System will be used at the baseline and day 3, day 7, day 10 and day 14 of the drug intervention. It is a checklist covering 4 main, 7 secondary and 13 accompanying items. These items are the symptoms and signs summarized by experts according to the clinical manifestations of COVID-2019[24]. The main items consisting of fever, coughing, fatigue and short breath use a four-point scale (0, 2, 4 and 6) depending on the severity; the 7 secondary items including dysphoria, diarrhea, pharyngalgia, expectoration, muscular soreness, nasal obstruction and rhinorrhoea use 0-3-point scale; the 13 accompanying items contain chest pain, headache, aversion to cold, dizziness, nausea and vomiting, anorexia, abdominal distension, dry mouth, anxiety, spontaneous sweating, insomnia, wheezing and blood tinged sputum, and each item is rated on 0-1 scale ( 0 stands for asymptomatic, 1 stands for symptomatic ). The total scores sum up to a range from 0 to 58, with higher scores indicating more severe levels of disease.

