***Safety outcomes***

Test safety will be monitored during this trial. Participants will accept a routine physical examination, including breath rate, heart rate, temperature, blood pressure, weight, routine urine test, routine blood test, liver, kidney function tests, and an electrocardiogram.

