**STATISTICAL ANALYSIS**

We will use log-rank test for the primary outcome, if the influence of confounding factors needs to be considered, Cox proportional hazard model can be used. For all secondary outcomes, Wilcoxon rank sum test will be used. For safety evaluation of TCM, two-sided t-test will be applied to each safety measurement after data normalization.

To better understand the nature the missing mechanisms, we will characterize the type of subjects who have missing data, then statistical models to impute missing values if the assumption of missing at random is met will be used.

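### The protocol gives no control-arm comparator for symptomatic harm: adverse events are tied to the decoction by definition, the tested safety measurements contain no symptoms, and the TCM score counts new symptoms only as disease

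*Protocol*

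**What the plan says.** **The score.** The protocol's section on the TCM Syndrome Scoring System describes a 24-item form: "It is a checklist covering 4 main, 7 secondary and 13 accompanying items". The main items are scored in steps of two: "The main items consisting of fever, coughing, fatigue and short breath use a four-point scale (0, 2, 4 and 6) depending on the severity". Diarrhoea is a secondary item: "the 7 secondary items including dysphoria, diarrhea, pharyngalgia, expectoration, muscular soreness, nasal obstruction and rhinorrhoea use 0-3-point scale". Nausea and vomiting, anorexia, abdominal distension, dry mouth, dizziness and insomnia are accompanying items scored 0 or 1: "the 13 accompanying items contain chest pain, headache, aversion to cold, dizziness, nausea and vomiting, anorexia, abdominal distension, dry mouth, anxiety, spontaneous sweating, insomnia" (the list continues). All items are summed and read in one direction: "The total scores sum up to a range from 0 to 58, with higher scores indicating more severe levels of disease". Nothing separates a symptom present at D0 from one that starts on treatment. Fig. 2 schedules the form at D0, D3, D7, D10 and D14 and at both follow-up visits, with no distinction between arms.

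**Safety measurements.** The Safety outcomes section reads: "Participants will accept a routine physical examination, including breath rate, heart rate, temperature, blood pressure, weight, routine urine test, routine blood test". It goes on to liver and kidney function tests and an electrocardiogram. No symptom is listed.

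**Adverse events.** The section on adverse event reporting does include symptoms, but only those related to administration of the decoction. The researchers judge that relationship. Fig. 2 lists adverse events among the safety outcomes on D1 to D14 and at both follow-up visits.

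**Analysis.** The Statistical Analysis section reads: "For all secondary outcomes, Wilcoxon rank sum test will be used. For safety evaluation of TCM, two-sided t-test will be applied to each safety measurement". It names no method for event counts.

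**The concern.** The Abstract and Background give efficacy and safety as the aims. For an oral treatment added to routine care, new digestive or sleep symptoms are an obvious safety question, and some of them also occur in COVID-19. Only a comparison with the control arm can separate the two sources. The plan has three places where such a symptom could appear, and none of them gives that comparison:

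- The tested safety measurements do not contain it.
- The adverse event record accepts it only if it is attributed to the decoction, so the control arm has no count to set beside it.
- The TCM score records it in both arms, but only as a contribution to disease severity, where improvement in a main symptom can offset it.

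At stake is the safety conclusion. An adverse event rate in the TCM arm with no control rate cannot be interpreted. It could overstate harm, because background symptoms are attributed to the decoction. It could also understate harm, because new symptoms are attributed to COVID-19. According to the Blinding section, the clinical therapists know the allocation.

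**Working it through.** **1. The plan's own figure.** Inputs are from the TCM Syndrome Scoring System section: 4 main items with maximum 6, 7 secondary items with maximum 3, and 13 accompanying items with maximum 1.

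4 × 6 + 7 × 3 + 13 × 1 = 24 + 21 + 13 = 58. The stated maximum is reproduced.

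**2. Size of the possible offset.** The digestive items are diarrhoea (3), nausea and vomiting (1), anorexia (1) and abdominal distension (1).

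- Maximum: 3 + 1 + 1 + 1 = 6 points, and 6 / 58 = 10.3% of the range.
- One main symptom going from worst grade to absent: 6 − 0 = 6 points, so the two can cancel exactly.
- A smaller case: new grade-2 diarrhoea (+2) and a one-step improvement in cough (−2) sum to 0.
- Limit: the main items together carry 24 points, so the offset is only partial when several of them improve. The full 6 points also require grade-3 diarrhoea and all three other digestive items in the same patient.

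**3. Where could a new symptom be compared between arms?**

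| Record | Holds these symptoms? | Control-arm comparator? |
|---|---|---|
| Safety outcomes, tested by t-test | No | Yes, but for other measurements |
| Adverse events | Yes, if related to the decoction | No, excluded by definition |
| Rate of symptom recovery | No, four main symptoms only | Yes, but not for harm |
| TCM score | Yes, whatever the cause | Only inside the total |

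The last row is the only one that holds the data needed.

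**4. Illustration of what the total can and cannot show.** The event rates and score distribution below are assumptions; the documents give none. With 70 per arm and the planned 10% dropout, 70 × 0.9 = 63 per arm remain.

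Take new diarrhoea in 20% of TCM and 5% of control patients, with grades 1 to 3 equally likely (mean grade 2). The mean shift in the total is (0.20 − 0.05) × 2 = 0.30 points. Against a base score with mean 8 and SD 4 to 8, truncated at 0, simulation gives the rank sum test on the total about 6% power, hardly above its 5% error rate.

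Power of Fisher's exact test on the single item, 63 per arm, two-sided 5%, uncorrected:

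| TCM v control | Power |
|---|---|
| 20% v 5% | about 66% |
| 15% v 5% | about 35% |
| 20% v 10% | about 26% |
| 10% v 5% | about 10% |

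With a Bonferroni correction for 7 + 13 = 20 items, the first row falls to about 25%. These figures do not justify formal item-level testing. They support reporting an estimate with its interval. At 20% v 5% the risk difference is 15 percentage points, with an approximate 95% half-width of 1.96 × √(0.20 × 0.80 / 63 + 0.05 × 0.95 / 63) = 0.112, or about 11 points.

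**The case against.** Most of the case on the other side is sound, and it sets the limits of this point.

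- **Symptoms are a safety outcome.** They fall under the adverse event definition and are scheduled daily. A reader might infer that symptomatic harm is never compared between arms, or that the trial would report no difference and call the decoction safe. The documents do not support either reading. Diarrhoea attributed to the decoction would be recorded, and all score items are compared between arms within the total.
- **Benefit is not hidden.** The Rate of symptom recovery section is a separate secondary endpoint on fever, cough, malaise and shortness of breath. New diarrhoea cannot offset it. This stands, so a separate main-item subtotal is optional.
- **The score is used as designed.** Its items were chosen as manifestations of COVID-19, and every summed score lets items offset one another. Including them is not an error.
- **No harm is shown.** No section says that the decoction causes these symptoms. The harm is a possibility that a safety assessment should be able to examine.
- **By-arm tables belong in the statistical analysis plan.** This is true of the table layout. But an analysis plan cannot tabulate control-arm events that the protocol's definition excludes from collection, and that definition is protocol content.
- **The definition may be looser in practice.** The researchers are to assess the relationship of events to the study drug, which suggests that events are noted before attribution. If so, the definition should say so. As worded, relatedness is a condition of being an adverse event.
- **Item counts are not a clean measure of harm.** They include the ordinary course of COVID-19 and partly come from unblinded patients' own reports. Randomisation handles the first on average but does not remove the second.

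**Conclusion.** The concern holds in a limited form: the protocol specifies no control-arm comparator for symptomatic harm. This follows from three texts read together, the relatedness condition in the adverse event definition, the symptom-free list of safety measurements, and a symptom score used only as a disease total. It does not depend on the simulation or on any assumed event rate.

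The part that can be sized from the documents is modest: up to 6 of 58 points (10.3%) for the digestive items, equal to one main symptom resolving completely. The power figures are illustrative. They range from about 10% to 66% for an uncorrected single-item test over the assumed differences, and the contrast with about 6% for the total rests on one assumed scenario.

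The primary outcome and the validity of the total as a severity score are unaffected. What changes is the safety conclusion the trial can support. The change should be made, because the score data are already scheduled in both arms and the adverse event definition can be corrected in a sentence.

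**What to change.** 1. **Adverse event section:** define adverse events irrespective of cause, collect them in the same way in both arms, and keep the judgement of relatedness as a separate recorded item. Compare incidence by arm.
2. **Safety outcomes and Statistical Analysis sections:** add, from the TCM score forms, the number of participants per arm with each secondary and accompanying item new (0 at D0, at least 1 later) or worsened relative to D0. Give the risk difference with its 95% CI, report the digestive items together as well, and state that the table is read descriptively.
3. **TCM score:** keep the total and its rank sum test as planned. A main-item subtotal (0 to 24) is optional.

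**Cost:** the item table uses forms already scheduled in both arms and needs no new visits, patients or procedures. The wider definition means recording more events, including in control patients. Recruitment began in March 2020, before this protocol version, so control-arm events may be incomplete for participants already enrolled; the item table does not have that gap where the forms were completed. The downside is about 20 item-level comparisons that also count the natural course of COVID-19 and partly rest on unblinded self-report. The report should say so.

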**Coronavirus nucleic acid test**

The coronavirus nucleic acid test by reverse transcription polymerase chain reaction ( RT-PCR ) will be conducted at the baseline and day 3, day 7, day 10 and day 14 of the study intervention. The time ( in days ) of the respiratory tract sample and blood specimens SARS-CoV2 RT-PCR to be negative for two consecutive times based on the first testing time will be defined as primary outcome.

**Improvements of chest X-ray (CRX)**

An experienced radiologist who was blinded to the study allocation reviewed the chest computed tomography (CT) images from all patients. An improvement in CRX images was defined as a decreased area of infiltration, a decreased area of any radiologic abnormality, or decreased density of the ground-glass opacity or nodules.

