**Criteria for discontinuing**

1. The participant decides to discontinue the intervention, the trial or data collection at any time for any reason.
2. Non-compliant patient.
3. In the case of the onset of serious adverse events.
4. The aggravating pathology changes which require ventilator support for treatment during the intervention.

Participants discontinued the trial will be recorded throughout the intervention and followup periods, their data will be collected in the case report form. If the trial wouldn’t continue due to serious adverse events or aggravated illness, appropriate treatment will be taken.

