**Sample size**

Based on previous clinical practice of using TCM fought against SARS and H1N1 influenza patients [23], it is estimated the median survival time in the TCM group as 3 days, and 1.5 times longer in the control group. Concerning the analysis of the primary endpoint, the duration of time before improvement of at least one of the common cold-like symptoms (fever, cough, malaise, shortness of breath) , will be estimated using the Kaplan-Meier method, and

the survival curves will be compared between groups using the log-rank test. And this study is designed to detect a statistically significant difference with a level of 5% and a power of 70% (one-sided type-1 error of
[figure not shown]
 =5%，
[figure not shown]
 =30%), so approximately 61 participants in each group will be needed. Thus, under the prediction of a dropout rate of 10%, the sample size of 140 participants will be sufficient to detect a clinically important difference in this trial.

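### The imaging definition counts a patient as improved if any one abnormality shrinks or fades, with no condition on overall extent or on new or growing lesions

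*Protocol*

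**What the plan says.** Under MEASUREMENTS, the protocol lists chest imaging among the secondary outcomes. The section headed Improvements of chest X-ray (CRX) gives the rule: improvement means "a decreased area of infiltration, a decreased area of any radiologic abnormality, or decreased density of the ground-glass opacity or nodules". The second alternative is "a decreased area of any radiologic abnormality" and the third is "decreased density of the ground-glass opacity or nodules". The reading is described as follows: "An experienced radiologist who was blinded to the study allocation reviewed the chest computed tomography (CT) images from all patients".

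Three other places could bear on the rule:

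- Criteria for discontinuing lists "The aggravating pathology changes which require ventilator support for treatment during the intervention". This is a ground for stopping and is not linked to the imaging score.
- STATISTICAL ANALYSIS says "For all secondary outcomes, Wilcoxon rank sum test will be used". It names no categories for the imaging outcome.
- The outcome rows of Fig. 2 contain no imaging assessment.

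**The concern.** The criteria are joined by *or*, and the second and third each qualify alone. A mixed response (one lesion smaller or paler, another larger or new) therefore meets the definition as it stands. So does a fall in ground-glass area that occurs because the region has consolidated: one abnormality covers less area although the lung is no better. Nothing in the protocol makes worsening elsewhere override the score, and there is no category in which to record worsening.

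The outcome matters more than its secondary rank suggests. Patients and therapists know the allocation (Blinding), and cough and malaise are self-reported (Rate of symptom recovery). The blinded imaging read is the trial's direct view of the lung. If the rule admits mixed response and some net progression, a difference in the proportion improved cannot be taken as a difference in improvement of pneumonia.

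**Working it through.** **1. The rule, case by case.** The protocol states no rate, sample size or power for imaging, so there is no figure to reproduce. Reading the definition literally gives:

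| Change from baseline | Alternative met | Score under the rule |
|---|---|---|
| All abnormalities smaller or paler | any of the three | improved |
| One lesion smaller, another larger, net extent up | second | improved |
| One opacity paler, a new lesion present | third | improved |
| Ground-glass area down because it has consolidated | second | improved |

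Only the first row is clearly improvement of the pneumonia.

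**2. Search for an offsetting condition.** The stopping criterion applies only when ventilator support is needed and does not change a score. The analysis section names a test only. Fig. 2 schedules no imaging among its outcomes. No section requires stable remaining lesions, no new lesions or a lower total. The gap stands.

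**3. How often could it occur?** The protocol gives no data, so this is an illustration only. Assume *k* independent abnormalities, each shrinking with probability *q* and growing with probability *g*; new lesions are left out.

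- P(rule met) = 1 − (1 − q)^k
- P(some shrink, none grows) = (1 − g)^k − (1 − g − q)^k
- With k = 3, q = 0.20, g = 0.20: 1 − 0.8³ = 0.488 and 0.8³ − 0.6³ = 0.512 − 0.216 = 0.296. The remaining 0.488 − 0.296 = 0.192 of patients are scored improved while a lesion grows.
- With k = 2, q = 0.10, g = 0.20 the share is 0.04. With k = 5, q = 0.30, g = 0.40 it is 0.76.

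These are mixed readings, not necessarily net progression. The width of the range shows that the frequency is unknown.

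**4. What would it do to the comparison?** Assume true net-improvement rates of 60% and 40%, and add to each arm the mixed readings without net improvement.

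| Assumed mixed readings | Reported rates | Difference |
|---|---|---|
| none | 60% vs 40% | 20 points |
| 20% of patients in both arms | 80% vs 60% | 20 points |
| 25% of those not improved, both arms | 60 + 0.25 × 40 = 70% vs 40 + 0.25 × 60 = 55% | 15 points |
| 50% of those not improved, both arms | 60 + 0.50 × 40 = 80% vs 40 + 0.50 × 60 = 70% | 10 points |
| 10% vs 30% of patients | 70% vs 70% | 0 points |
| 30% vs 10% of patients | 90% vs 50% | 40 points |

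In the second row, 20/80 = 25% and 20/60 = 33% of those reported as improved have no net improvement. The risk ratio falls from 60/40 = 1.50 to 80/60 = 1.33. The odds ratio rises from (0.6/0.4)/(0.4/0.6) = 2.25 to (0.8/0.2)/(0.6/0.4) = 2.67. With 70 per arm, the unpooled z rises from 0.20/√(0.48/70) = 2.4 to 0.20/√(0.40/70) = 2.6. The direction thus depends on the assumed shares and on the scale used.

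**The case against.** **A sensible reader would judge the whole image.** The first alternative can be read as total infiltrated area, and the second as whatever type of abnormality the patient has, not any single lesion. This is fair: the text does not force every reader to score a mixed case as improved. But even on that reading, lower density qualifies alone whatever happens to area, and smaller ground-glass area qualifies even when it has turned into consolidation. Leaving the choice to one reader's discretion does not fix the endpoint.

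**The details belong to a reading form or the analysis plan.** That holds for measurement thresholds and the handling of reading variation, so their absence is not counted here. It does not hold for the definition itself, which the protocol states and which a later document would inherit.

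**The outcome claims improvement, not recovery.** This is correct. The protocol requires complete resolution only for symptoms. A lenient rule makes the endpoint non-specific; it does not make it meaningless.

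**What a reader might wrongly infer.** It is tempting to say that the rule dilutes the treatment effect or favours one arm. The documents support neither. With equal mixed shares the absolute difference is unchanged and the odds ratio rises. The assumption that erases the difference (10% vs 30%) was chosen to do so, and swapping the shares doubles it. The radiologist is blinded to allocation.

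**Conclusion.** The concern holds as a defect of definition. Read literally, the rule lets a patient with a mixed response, or with net progression, be scored as improved, and no other section prevents it. The imaging outcome therefore does not specifically measure improvement of pneumonia.

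This conclusion rests on the wording alone. How often such scoring would occur, and whether it would narrow or widen the difference between arms, cannot be determined from the protocol; every rate in the working is an assumption. The primary outcome and the sample size are not affected. The change is worth making because the endpoint is one of the few read blind, but it does not put the trial's main conclusion at risk.

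**What to change.** In the section Improvements of chest X-ray (CRX), replace the three alternatives with one overall classification by the same blinded radiologist, relative to the baseline image:

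- **Improved:** total extent or density of all abnormalities is lower.
- **Unchanged:** no overall change.
- **Worsened:** total extent or density of all abnormalities is higher.
- **Mixed cases** are assigned by the net change in total extent. Large overall clearing with one small new focus can then still count as improved.
- A fall in ground-glass area caused by **conversion to consolidation** does not count as improvement.
- **New or enlarging lesions** are recorded separately.

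Compare the three ordered categories with the rank sum test already planned for secondary outcomes.

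The cost is a short change of text and a few fields on the reading form. Because the rule refers to a baseline image, the section must also say which images are compared; at present it gives no time point. Improvement rates will probably be lower. The section is written in the past tense, and version 2.0 is dated October 2020 although recruitment began in March 2020, so some images may already have been read. Any such images need a blinded re-read by the same radiologist, with a documented amendment before unblinded analysis.

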**Rate of symptom recovery**

The rate of symptom (fever, cough, malaise, shortness of breath) recovery will be one of the secondary endpoints. Fever denoted the subaxillary temperature being 37 degrees or greater. The cough and malaise was self-reported by the patients. Recovery of symptoms will be defined as the complete resolution of fever, cough, malaise, shortness of breath.

***Safety outcomes***

Test safety will be monitored during this trial. Participants will accept a routine physical examination, including breath rate, heart rate, temperature, blood pressure, weight, routine urine test, routine blood test, liver, kidney function tests, and an electrocardiogram.

***Adverse event reporting and treating***

Adverse events (AEs) will be defined as unpredictable, undesirable symptoms, signs or diseases related to the administration of maxingshigan-weijing decoction and will be recorded and managed by the researchers during the treatment period. The researchers will scrupulously evaluate the relationship between these adverse events and the experimental drugs, then manage them quickly and properly. Furthermore, patients will be continuously followed up until their condition returns to normal. Participants who might be injured during the study will get a financial compensation.

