Faced with COVID-2019, because of no clinically specific drugs currently[19], doctors choose the drugs mentioned above empirically but the clinical efficacy is unsatisfactory and uncertain. During these challenging and unprecedented times, the current clinical guideline in China suggest both conventional medicine and TCM should be used for the treatment of patients with infection of SARS-CoV-2[20].

Based on these evidence and experience, there is a general expectation that TCM would be a valuable weapon in the armory against SARS-CoV-2. So an open-label, multicenter randomized controlled study will be carried out to evaluate the efficacy and safety of Traditional Chinese Medicine in treating COVID-2019. This study is conducted in Wenzhou city, Zhejiang Province, because Wenzhou is one of the worst-hit cities outside hubei province by COVID-2019.

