**METHODS**

**Study design**

This is an open-label, multicenter, randomized controlled, comprehensive treatment clinical study, with outcome assessors and data analysts blinded to the group assignment. Eligible participants with Mild and Moderate Pneumonia caused by SARS-CoV-2 will be randomly assigned to either the experimental ( Traditional Chinese Medicine + Routine supportive care ) or the control group ( Routine supportive care ) in an equal proportion. Routine supportive care remains the major treatment, including the therapies of anti-viral, anti-bacterial and ameliorating the related symptoms[21]. The study consisted of three phases: a screening period, a treatment period of 14 days, and a follow-up period of 2 weeks. Fig. 1 briefly shows the study flow chart, and Fig. 2 enumerates the treatment schedule and outcome measures. The study adheres to the Standard Protocol Items: Recommendations for Intervention Trials (SPIRIT 2013) checklist [22].

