**Randomization**

Minimization method will be used, with balancing of the arms with pneumonia severity. Patients are randomized (1:1 ratio) to each group. Clinical researchers will get a random sequence number which is automatically generated by a random number generator (IBM Corp., Armonk, NY, USA), and sequentially number them in an opaque envelope. Researchers will open random allocation envelopes and assign participants accordingly. Eligible patients will be randomly divided into a routine supportive care group and a routine supportive care plus oral administration of traditional Chinese medicine group, with 70 patients in each group.

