| **Safety outcomes** |  |  |  |  |  |  |  |  |  |  |  |  |  |  |  |  |  |
| Routine inspection | × |  |  | × |  |  |  | × |  |  | × |  |  |  | × | × | × |
| Urine routine test | × |  |  | × |  |  |  | × |  |  | × |  |  |  | × | × | × |
| Blood rne test | × |  |  | × |  |  |  | × |  |  | × |  |  |  | × | × | × |
| Biochemical test | × |  |  | × |  |  |  | × |  |  | × |  |  |  | × | × | × |
| Electrocardiogram | × |  |  | × |  |  |  | × |  |  | × |  |  |  | × | × | × |
| Adverse events |  | × | × | × | × | × | × | × | × | × | × | × | × | × | × | × | × |

**Fig.2** SPIRIT schedule for enrollment,treatment and assessments.

D day,TCM Traditional Chinese Medicine

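### Adverse events are defined as related to the decoction, so control patients can have none and adverse event incidence cannot be compared between arms

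*Protocol*

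**What the plan says.** The Background gives the purpose of the trial as "to evaluate the efficacy and safety of Traditional Chinese Medicine in treating COVID-2019". Under Adverse event reporting and treating, the protocol states: "Adverse events (AEs) will be defined as unpredictable, undesirable symptoms, signs or diseases related to the administration of maxingshigan-weijing decoction". These events "will be recorded and managed by the researchers during the treatment period". The next sentence adds: "The researchers will scrupulously evaluate the relationship between these adverse events and the experimental drugs".

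Study design gives the experimental arm the decoction plus routine supportive care and the control arm routine supportive care alone. Randomization is 1:1, "with 70 patients in each group".

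The Fig. 2 schedule has a row labelled "Adverse events", marked daily from D1 to D14 and again at both follow-up visits (D7 and D14). The row is not restricted to one arm.

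Apart from adverse events, Safety outcomes lists vital signs, weight, urine and blood tests, liver and kidney function and ECG for participants generally. Statistical Analysis plans a two-sided t-test on each safety measurement.

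**The concern.** An adverse event is normally any unwanted occurrence after randomisation, with causality judged as a second step. That order lets a randomised trial separate the effect of treatment from the background of the disease and its usual care. Here causality is a condition of entry. Patients who never take the decoction cannot meet it, so the concurrent control is lost for this outcome.

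Two errors become possible, in opposite directions. Harm can be hidden, because an event judged unrelated, or one that could have been foreseen, is not an adverse event at all. Harm can also be created, because whatever is recorded in the decoction arm is set against a control count that is zero by rule.

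A statistical analysis plan cannot repair this. It can analyse only what was collected under the protocol's definition.

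**Working it through.** The plan states no figure for adverse events, so there is none to reproduce. The main check sets the protocol's statements side by side.

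1. **Definition against arms.** An event must be unpredictable and related to the decoction. Controls receive no decoction (Study design). Possible control adverse events: 0 of 70.
2. **Definition within the decoction arm.** Events due to COVID-19, to antivirals or antibiotics, or to anything else unrelated are excluded. So are foreseeable reactions, because of the word unpredictable.
3. **Definition against the next sentence.** Relatedness is required for an event to count, and is then to be evaluated for the events that count. The two steps are circular.
4. **Window.** The text records adverse events in the treatment period. Fig. 2 also marks them at follow-up D7 and D14. The promise to follow patients until recovery covers events already recorded, not new ones.
5. **What does not depend on the definition.** Fig. 2 schedules routine inspection, urine, blood and biochemical tests and ECG at D0, D3, D7, D10, D14 and both follow-up visits.

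**Illustration of the consequence.** The plan names no test for adverse event counts; Fisher's exact test is used here as an example.

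- For x of 70 against 0 of 70, the two-sided p-value is 2 × C(70, x) / C(140, x).
- x = 5 gives p = 0.058 and x = 6 gives p = 0.028, so six recorded events are enough for nominal significance at 5%.
- Assume that both arms have the same true event rate p and that a share f of decoction-arm events is called related. The recorded count is then binomial(70, p × f), and the chance of a false excess is P(X ≥ 6).

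| True rate p in both arms | f = 0.25 | f = 0.5 | f = 1 |
|---|---|---|---|
| 10% | 0.8% | 13.7% | 71.3% |
| 20% | 13.7% | 71.3% | 99.7% |
| 30% | 42.9% | 96.2% | about 100% |

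Both p and f are assumptions; neither is in the protocol. The loss runs the other way too. At p = 20% and f = 0.5, 70 × 0.20 × 0.5 = 7 decoction-arm events would be expected to be dropped as unrelated.

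**The case against.** The strongest reply is that safety does not rest on adverse events alone. The Abstract names laboratory testing before and after treatment as the means of assessing safety. The laboratory, vital-sign and ECG data come from participants in both arms, and the planned t-tests do not use the adverse event definition. This stands. A reader might infer that the trial cannot compare safety at all, and the protocol does not support that. Statistical Analysis does not say whether the t-tests are between or within arms, but the data for a between-arm comparison will exist. Mean differences in measurements still do not count clinical events.

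Second, some control events will be captured anyway. Criteria for discontinuing covers any participant who worsens to the point of needing a ventilator and has discontinued participants' data entered in the case report form. The Fig. 2 row also covers both arms. This stands too, so it would be wrong to say that every control event goes unrecorded. Multiplying an assumed background rate by 70 (20% to 40% gives 14 to 28 patients) would not measure the loss, because the protocol gives no rate and actual practice may follow Fig. 2.

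Third, the sentence on evaluating relatedness suggests loose drafting, with events meant to be recorded first and judged afterwards. That is plausible, but the definition as written says otherwise, and the staff completing the forms need one rule.

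A reader might also infer that unblinded staff make the causality judgement. The text says only that researchers do. Blinding unblinds patients and therapists and blinds outcome assessors, and it does not say which group classifies adverse events. Bias from knowledge of allocation is therefore a risk, not an established fact.

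**Conclusion.** The definition is wrong as written. It fixes the control adverse event count at 0 of 70 and filters the decoction-arm count by causality and expectedness, so adverse event incidence cannot be validly compared between arms. This follows from the wording alone and needs no assumed rate. The false-excess probabilities, from 0.8% to nearly 100%, only illustrate how far the result would depend on the share of events called related.

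The conclusion is limited to adverse event incidence. The laboratory, vital-sign and ECG comparisons remain available, and the primary endpoint, sample size and randomisation are untouched. The conflict over when relatedness is judged and the conflict over the recording window are separate inconsistencies in the text, and both need to be reconciled.

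**What to change.** Amend Adverse event reporting and treating as follows:

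- Define an adverse event as any untoward medical occurrence after randomisation in either arm, whatever its cause and whether or not it was expected.
- Record relatedness afterwards as a separate field, and state who judges it.
- Collect adverse events in the same way in both arms over the window in Fig. 2 (D1 to D14 and both follow-up visits), and make the text agree with it.
- Report the number and percentage of participants with any adverse event and with any serious adverse event, by arm.
- Check that the use of serious adverse events under Criteria for discontinuing is consistent with the revised definition.

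Trial status dates this version October 14, 2020, with recruitment from March 2020, so some patients may already have been handled under the present wording. Any retrospective capture from inpatient notes should be applied in the same way to both arms and reported separately from prospective data. Back-filling the control arm only would set retrospective control data against prospective decoction data and introduce a new bias.

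The cost is an amendment and slightly more case report form entry. All participants are inpatients under close observation and Fig. 2 already schedules daily adverse event recording, so no extra visits are needed. The sample size stays at 140.
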